### Statistical analysis

#### Sample size

A target sample size of 100 person with dementia-carer dyads has been estimated to provide over 80% power to detect a moderate effect size (Cohen’s d = 0.3) difference at a significance level of 0.05 (two-sided), assuming a medium within-subject correlation (ρ = 0.5) between pre- and post-intervention measures.

#### Outcome analyses

The difference in outcome measures before and after intervention will be examined using a paired *t*-test at a significance level of 0.05 (two-sided). To control for covariates (NPI severity, dementia severity) linear mixed models will be used.

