The level of burden experienced by carers can be influenced by a myriad of factors. Behavioural and psychological symptoms of dementia (BPSD) (e.g., aggression, agitation) have been shown to be associated with carer burden (Black and Almeida 2004; Donaldson et al. 1998). Moreover, carers who reported lower satisfaction with the social support they receive or had greater reactions to the person with dementia’s behavioural problems had more symptoms of depression (Mittelman et al. 2008). The association between severity of the illness (either cognitive or functional impairment) and carer burden, however, was weak (Brodaty and Hadzi-Pavlovic 1990). Carer outcomes may also be influenced by the specific coping strategies used or the level of self-efficacy (Saad et al. 1995; Kneebone and Martin 2003; Fortinsky et al. 2002; Gilliam and Steffen 2006).

Adverse carer outcomes can lead to adverse outcomes in people with dementia. For instance, high levels of carer burden is a consistent significant predictor of institutionalisation (Yaffe et al. 2002; Gaugler et al. 2003; Hébert et al. 2001), and carer psychological morbidity was also a significant predictor of mortality of the care recipient (Brodaty et al. 1993). Therefore, carer interventions may benefit both the carer and the person with dementia. Carer interventions have significant but modest effects in improving carer knowledge, reducing carer burden, reducing psychological morbidity and delaying institutionalisation (Brodaty et al. 2003; Pinquart and Sörensen 2006). There is evidence that these effects can be maintained for up to 11 months post-intervention (Pinquart and Sörensen 2006). In particular, a 10-day Prince Henry Hospital residential carer training program proved effective in delaying residential care placement, delaying mortality, reducing carer’s psychological morbidity and lowering care costs (Brodaty and Gresham 1989; Brodaty and Peters 1991; Brodaty et al. 1993, 1997). These results suggest that carer training provided early in the course of dementia has significant benefits on the outcomes of people with dementia, and therefore such intensive carer training programs should be made more extensively available.

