#### Missing data

Patterns of missing data will be examined to identify potential biases. Where applicable, missing items will be handled as suggested in the literature for that particular instrument.

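### The before/after comparison rests on a paired t-test that drops every dyad without the follow-up score, so K-10 and burden changes are at risk of selection bias if loss is related to the scores

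*Protocol article*

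**What the plan says.** All places are in the protocol article.

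- **Outcome analyses**, main comparison: "The difference in outcome measures before and after intervention will be examined using a paired" *t*-test, two-sided at 0.05.
- **Outcome analyses**, next sentence: "To control for covariates (NPI severity, dementia severity) linear mixed models will be used". Covariate control is the only purpose given.
- **Missing data**: "Patterns of missing data will be examined to identify potential biases". Missing items are then to be handled by each instrument's published rules. Neither step acts on a visit that is missing altogether.
- **Sample size**: the target of 100 dyads "has been estimated to provide over 80% power" for d = 0.3 with a within-subject correlation of 0.5. No allowance for loss is mentioned.
- **Background**: "high levels of carer burden is a consistent significant predictor of institutionalisation", and "carer psychological morbidity was also a significant predictor of mortality of the care recipient". For behavioural and psychological symptoms (BPSD) it reports only an association with carer burden.
- **Assessment**: outcome measures are planned at baseline, 6 months and 12 months. No rule ends assessment at placement.

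**The concern.** A paired *t*-test is a complete-case analysis. It estimates the mean change among dyads seen at both visits. This equals the change in the enrolled group only if being seen is unrelated to the change in score. The Background gives reason to doubt that here, since carer burden and distress are tied to placement and death, events that may interrupt follow-up. Measures of the person with dementia cannot be taken after death at all.

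The answer on the primary outcome could therefore describe the dyads that stayed. If carers who were most distressed at baseline are lost, a real benefit is understated. If carers who got worse are lost, a reduction can appear where there is none. With a single arm, there is no control group in which similar losses might cancel. The test also discards baseline and 6-month scores from dyads without a 12-month score, although those data will have been collected.

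**Working it through.** **Step 1: the plan's own figure.** Inputs from Sample size: n = 100, d = 0.3, ρ = 0.5, two-sided α = 0.05.

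- Standardised paired difference: dz = d/√(2(1-ρ)) = 0.3/√1 = 0.30.
- Normal approximation: Φ(0.30·√100 - 1.96) = Φ(1.04) = 85.1%. The noncentral *t* gives 84.4%. The stated power of over 80% is reproduced.
- Pairs needed for 80% power: (2.80/0.30)² = 87.2, so 88 by the normal approximation, or 90 by the *t* distribution. About 10% loss is affordable even if it is random.
- Power under purely random loss: 80.4% at 90 pairs, 75.5% at 80, 69.7% at 70, 62.8% at 60.

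**Step 2: assumptions for selective loss.** The article gives no attrition rate or mechanism, so all of these are assumed: 20-30% of 12-month scores missing, and loss following a logistic model with an odds ratio of 1.5 to 2 per SD. Scores have SD 1 and correlation 0.5 between all visits, with 100 dyads and 6,000 simulated trials per scenario.

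**Step 3: loss driven by baseline distress, true change -0.30 SD.** If completers' mean baseline is shifted by m (negative when distressed carers are lost), their mean change is -0.30 - (1-ρ)m, which is nearer zero.

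- 20% lost, odds ratio 1.5: paired estimate -0.26. Power is about Φ(0.259·√80 - 1.96) = Φ(0.36) = 64%; simulated 62-63%.
- 30% lost, odds ratio 2: paired estimate -0.21. Power is about Φ(0.206·√70 - 1.96) = Φ(-0.24) = 41%; simulated 40-41%.
- A repeated-measures likelihood model on the same data is unbiased, with power of 77-80% and 74%. Its power was computed with the empirical SD, so it is approximate.

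Not all of the power loss is bias. In the first case power goes from 84.4% to 75.5% through fewer pairs alone, then to about 63% through selection. In the second it goes from 84.4% to 69.7%, then to about 41%.

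**Step 4: loss driven by worsening from baseline to 6 months (odds ratio 2), no true change.**

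- 20% lost: paired estimate -0.064. False reductions: Φ(0.064·√80 - 1.96) = Φ(-1.39) = 8.2%; simulated 8.1-8.2%.
- 30% lost: paired estimate -0.094. False reductions: Φ(0.094·√70 - 1.96) = Φ(-1.17) = 12%; simulated 11.4-11.7%.
- The nominal rate in that direction is 2.5%. The repeated-measures model is unbiased here, with a rate of about 2.5%.

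**Step 5: loss driven by the unseen 12-month score (odds ratio 2).** With three visits and true change -0.30 SD or zero, the paired bias is about -0.064 SD at 20% loss and -0.095 at 30%. The repeated-measures model is worse, at about -0.087 and -0.130. The reason is that if completers' 12-month mean is shifted by m, their own baseline is shifted by ρm, so the paired difference carries (1-ρ)m = 0.5m. The model restores the full baseline mean and carries about (1-R²)m. Here R² = 2(0.25)/(1.5) = 1/3, giving about 0.67m.

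**Step 6: wider range.** With two visits, 10-40% loss, odds ratios of 1.5 to 3 and true change -0.30 SD:

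| Loss driven by | Paired bias (SD) | Likelihood-model bias (SD) |
|---|---|---|
| Baseline score | +0.02 to +0.18 | about 0 |
| Follow-up score | -0.02 to -0.18 | -0.03 to -0.28 |

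Loss unrelated to the scores gives a bias of about zero for both.

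**The case against.** The strongest reply has four parts.

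1. **No loss is documented.** A reader might infer from the Background that results will be biased, or from the hypothesis of at least 60% still at home at 12 months that up to 40% will be lost. The article supports neither. It gives no attrition rate, and placement is not a missing visit: assessment is planned at every time point, time to placement is itself an outcome, and the Background says burden can persist for up to two years after admission. K-10 and burden can still be measured then. This stands, so the point is a risk and not a prediction.
2. **Direction and BPSD.** The Background fits loss of highly burdened carers best, which would understate benefit. Nothing in it says that dyads who worsen drop out, so the false-positive scenario is an assumption. A reader might also infer that the BPSD result is distorted in the same way, but the text links BPSD only to burden, not to placement or death. This stands too; what remains for BPSD is that scores do not exist after death.
3. **A mixed model is already planned, and neither analysis is called primary.** That is true, and the model could retain dyads with a missing visit. But the 0.05 level and the before/after question are attached to the paired test, and the model is given another purpose.
4. **Missing-visit methods often sit in the analysis plan or full protocol.** Their absence from an article is no fault. The point rests on the test that the article does name.

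The mixed model is also no cure in itself, as Step 5 shows. That limits the fix and does not remove the point.

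**Conclusion.** The point holds in conditional form. The stated test is complete-case, and nothing else in the stated plan changes the before/after estimate when a visit is missing. The Background makes score-related loss plausible for carer distress and burden. Under an assumed 20-30% loss that depends on observed scores, a true -0.30 SD is estimated as about -0.26 to -0.21 SD, or a null effect gives about 8-12% false reductions against 2.5%. The direction is undetermined, and with little loss or loss unrelated to the scores the bias is negligible. The claim that the mixed model removes the bias should not be made without its condition: it does so when loss depends on observed scores, and it can be further off than the paired test when loss depends on unseen 12-month scores. The change is worth making because it reuses data and a class of model already planned.

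**What to change.** In Outcome analyses:

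- Make the main analysis of each repeatedly measured score one linear mixed model for all dyads with a baseline score. Baseline, 6-month and 12-month scores are the repeated outcome, visit is categorical, and the within-dyad covariance is unstructured. Take the 6- and 12-month changes with 95% confidence intervals from it.
- Keep the paired *t*-test as a completers-only sensitivity analysis.
- Add a sensitivity analysis that shifts unobserved 12-month K-10 scores upwards in steps until the conclusion changes. This is a necessary part of the fix.
- For outcomes of the person with dementia, do not model scores after death; report the number of deaths beside the result.

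The cost is wording, one extra sensitivity table, and reliance on a missing-at-random assumption that must be stated. No extra data or dyads are needed. With complete data the model's estimate equals the mean paired difference, so nothing is lost if follow-up is full.

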#### Missing data

Patterns of missing data will be examined to identify potential biases. Where applicable, missing items will be handled as suggested in the literature for that particular instrument.

### Ethics

This study has been approved by the Human Research Ethics Committee, University of New South Wales, Sydney, Australia (Approval No.: #HC13033). Written consent will be obtained from all participating people with dementia and their primary carers. In the case where the person with dementia is deemed unable to provide informed consent, a responsible person will provide written consent and verbal assent will be obtained from the person with dementia.

## Discussion

*Going to Stay at Home* is a 7-day residential carer training program, which was adapted for use in residential aged care settings from a successful hospital-based residential carer training program. The present study aims to evaluate the effects of this program. Outcomes for carers and people with dementia will be measured using standardised instruments. In addition, qualitative analyses of interview and focus group data will be carried out to determine which components of the program carers found most effective and the impact of the program on practices within the residential aged care facility. This evaluation study will provide evidence for whether the program is effective in reducing carer psychological distress and burden as well as delaying institutionalisation of the person with dementia, which may have important implications for policy.

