**Discussion:**

This study will provide evidence on the effectiveness of the program in reducing carer distress and burden as well as delaying institutionalisation of the person with dementia, which may have important implications for policy.

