Residential respite care is defined as alternative, short-term care in a residential aged care facility (RACF) with the main purpose of providing the family carer with respite and support. The use of residential respite care has steadily increased in Australia, but take up rates remain low, with only 32% of eligible people with dementia accessing residential respite care services within 12 months of gaining approval (AIHW 2012). There appears to be little empirical support for the efficacy of residential respite care, with some studies even reporting adverse effects on people with dementia, such as an increase in problem behaviours and earlier institutional placement (Brodaty and Gresham 1992). However, anecdotal reports from carers suggest residential respite care may have significant benefits provided carers are well informed and the most appropriate services are utilised. Residential respite care can provide an opportunity to combine existing knowledge about carer interventions with respite.

The principal aim of this study is to evaluate, in an open single-arm trial, the effects of the *Going to Stay at Home* program, which is adapted from the Prince Henry Hospital program for use with residential respite.

It is hypothesised that:carer psychological distress will be reduced at 6- and 12-month follow-up compared to baseline,carer burden will be reduced at 6- and 12-month follow-up compared to baseline,there will be no increase in BPSD in the person with dementia, anda minimum of 60% of carers will have the person with dementia still living at home at 12-month follow-up.

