## Methods/Design

### Study design

A single-arm longitudinal design will be used. Data will be collected at three time points: at the start of the residential program (baseline), at 6 months (post 1) and at 12 months (post 2) after completion of the program.

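### The Abstract and Discussion promise evidence that the program is effective and delays institutionalisation, but a single-arm study with no comparison rate can only describe change from baseline and the share still at home

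*Protocol article*

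**What the plan says.** The article is open about its design. The Background sets out to evaluate, "in an open single-arm trial, the effects of the" program, and Study design states "A single-arm longitudinal design will be used". The four hypotheses in the Background are mostly descriptive. Distress and burden are to be lower at 6 and 12 months than at baseline, behavioural symptoms are not to increase, and at least 60% of carers are to have the person with dementia still at home at 12 months.

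Outcome analyses names a paired t-test of before against after, and linear mixed models adjusting for neuropsychiatric symptoms and dementia severity. Outcome measures defines time to placement as days from recruitment, in this one cohort.

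The summary statements go further. The Abstract makes this promise: "This study will provide evidence on the effectiveness of the program in reducing carer distress and burden as well as delaying institutionalisation". The closing Discussion says the evidence will bear on "whether the program is effective in reducing carer psychological distress and burden as well as delaying institutionalisation of the person with dementia". Both add that this may matter for policy, and neither states a limit that follows from having no control group.

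**The concern.** To say that a program is effective, or that it delays placement, is to say that outcomes differ from those the same dyads would have had without it. The article describes no concurrent, waiting-list or historical group that could stand for that alternative. The earlier hospital program is cited as background and as the source of the adaptation, not as a comparator. The covariate models adjust within the cohort and do not supply one either.

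If the Abstract and Discussion are followed as written, a significant fall in the K-10 would be reported as effectiveness, and an at-home figure above 60% as delay. The reverse error is also possible: a flat K-10 could be reported as no effect when the program had held back a worsening. The Background gives a reason to take the placement claim seriously, since it reports that some studies of residential respite found earlier placement. The direction is thus an open question in the article itself, and this design cannot distinguish delay from hastening.

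**Working it through.** **1. The plan's own figure.** The inputs are from Sample size: "A target sample size of 100 person with dementia-carer dyads", effect size 0.3, two-sided 0.05, correlation 0.5.

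- Standardised paired difference: 0.3 / √(2 × (1 − 0.5)) = 0.30.
- Noncentrality: 0.30 × √100 = 3.0, with 99 degrees of freedom.
- Power: 84.4% by the noncentral t, 85.1% by the normal approximation.

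This agrees with the stated figure of over 80%. The sample size is not at fault. What it powers is detection of a mean change.

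**2. What the paired comparison estimates.** Write the mean change from baseline as

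observed change = program effect + change that would have occurred anyway.

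The paired t-test asks whether the left side is zero. The second term on the right is not measured anywhere in the design, so the first cannot be recovered. Two cases at the size of the design effect show this. They are chosen for illustration, and the documents give no value for the second term:

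| Observed change (SD) | Change anyway (SD, assumed) | Program effect (SD) |
|---|---|---|
| −0.30 | −0.30 | −0.30 − (−0.30) = 0 |
| 0 | +0.30 | 0 − 0.30 = −0.30 |

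The first row is a significant result with no program effect. The second is a null result with the full design effect.

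**3. Direction of the change that would have occurred anyway.**

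- Downward: baseline is taken at the start of the residential week, in dyads recruited through assessment teams, carer groups, hospitals and community care. Some may enter at a temporary high and settle afterwards.
- Upward: the Background reports that depression rose in carers under usual care and that carer burden rose over time.

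The documents give no K-10 mean or standard deviation and no distress threshold for entry. Neither force can be sized, and their net direction cannot be determined.

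**4. Placement.** Delay would be read from the at-home proportion, or from time to placement, set against an untreated rate. The article gives none.

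- If 60 of 100 dyads are at home at 12 months, all followed, the exact 95% interval is 49.7% to 69.7%.
- If 70 of 100 are at home, it is 60.0% to 78.8%.
- The chance of observing at least 60 of 100 is 18%, 54%, 87% and 99% when the true rate is 55%, 60%, 65% and 70%.

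These figures show how well the study can describe its own rate. They do not address delay. Against an assumed untreated rate of 50%, an observed 60% is 60 − 50 = 10 points better. Against an assumed 70%, it is 60 − 70 = 10 points worse. The benchmark is met in both cases.

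**The case against.** The strongest reply is that nothing is hidden. The single arm is declared, the hypotheses are already worded against baseline, the tests match them, and the two summary sentences promise evidence rather than proof. This stands in part: the operative text is sound, and the mismatch is confined to the Abstract and the Discussion. But the causal terms are the article's own, and those are the sentences that policy readers will use.

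A second reply is that a condensed article may leave the source of the 60% and the placement analysis to a fuller document. That is fair, and their absence is not counted against the plan here. An analysis plan could name an external rate, and the fix allows for that. It could not create a concurrent comparator in a single-arm study.

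A reader might infer something stronger: that regression to the mean alone explains the whole target effect, because with a correlation of 0.5 half of any entry elevation vanishes, so that 0.6 SD of elevation gives 0.5 × 0.6 = 0.30 SD. The documents do not support this, for four reasons.

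- One minus the correlation, times the elevation, applies when people are selected on a high observed score and elevation is measured from the source-population mean. A carer who is temporarily above their own usual level would be expected to return all the way. One who is persistently more distressed would not be expected to return at all. The fraction may lie anywhere from 0 to 1, and the correlation in Sample size is a planning assumption that does not fix it.
- The 0.6 SD is not in the documents. It is simply the value that gives back 0.30 SD, and the rejection rate it implies is the plan's own 84.4% power under another name.
- There is no distress threshold for entry, and the K-10 asks about the last four weeks rather than the day of arrival.
- The natural course cited in the Background runs the other way.

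**Conclusion.** The point holds as a mismatch between the stated conclusion and the design. For delay it needs no numerical assumption: the article gives no rate or group against which placement could be later. For effectiveness it rests only on the absence of any estimate of change without the program. Bias in either direction is possible, and its size and net sign cannot be derived from the documents, so no false-positive rate should be attached to it. Nor should a reader conclude that a fall in the K-10 would be spurious: it might be real, and the true benefit might exceed it. The sample size, tests and visit schedule are unaffected. What changes is what the trial may claim.

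**What to change.** Bring the Abstract and Discussion into line with the hypotheses in the Background. State the aim and the conclusion as (a) change from baseline in carer distress and burden at 6 and 12 months, and (b) the proportion of people with dementia still at home at 12 months, each with a 95% confidence interval. Remove effectiveness and delay as conclusions, and say plainly that change cannot be attributed to the program without a comparison group.

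If a statement about placement timing is wanted, name an external comparison rate before the data are seen, and justify that its population, dementia severity and follow-up are comparable. Even then, the claim would rest on that comparability.

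Adding a K-10 at recruitment would not solve the problem. The article gives no length for the wait before the program, so change over that wait would not be like-for-like with change over 6 and 12 months.

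The core change costs only wording, and the price is a weaker headline.
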